### Safety and adverse event monitoring

Adverse events will be systematically assessed and recorded by investigators throughout the trial, including during and up to 30 min after each tDCS session. Predicted adverse events specific to tDCS include itching, tingling, headache, burning, and discomfort at the stimulation site. In addition, adverse events related to post-stroke dysphagia-such as the pneumonia, enteritis, fever and abnormal breath sounds-will also be monitored.

All adverse events will be categorized as adverse device events (ADEs), serious adverse events (SAEs), and serious adverse device events (SADEs) and their incidence, number, and percentage per event will be documented. Events will be further standardized using the most recent version of the Medical Dictionary for Regulatory Activities (MedDRA), with reporting by System Organ Class (SOC) and Preferred Term (PT). These data will be analyzed and reported by group to ensure comprehensive safety monitoring throughout the study.

### Vital signs and physical examination

The vital signs will be assessed after 5 min of resting in a seated position by measuring systolic and diastolic blood pressure, pulse and body temperature. They will be assessed at Baseline, Mid-intervention and post-intervention.

The physical examination will be performed at Baseline, Mid-intervention, Post-intervention, and Follow-up. It includes assessing height, weight, skeletal muscle index, body mass index, body water, protein, minerals, and body fat percentage.

### Concomitant medications and clinical treatments

There are no specific restrictions on medication usage for the current trial. However, to minimize the impact of any medication on the intervention, the participants who are consuming medication must remain with a stable and unaltered treatment prescription for at least 1 week before screening to allow concomitant medication administration. Additionally, changes in the type of medication and dosage during trial participation are not allowed.

However, as some medications might affect the cough reflex (sedatives, pain medications, etc.), caution will be implemented before performing the VFSS test. A detailed record of the type of medication, dosage, and reason for taking the medication will be documented.

Swallowing rehabilitation treatment can be maintained during the clinical trial without interruption. The participant might be allowed to receive concomitant surgery, medication, or other medical device interventions that are not considered to influence the interpretation of the results. The method and number of swallowing rehabilitation treatments received during the clinical trial, the types and dosages of all concomitant medicines, etc. will be documented at each visit by the investigator and recorded in the case report form (CRF), as well as confirmed adverse events.

### Trial status

The recruitment of the participants is set to begin in March of 2024, and it is expected to be complete (including Follow-up testing) by May 2026.

## Discussion

The purpose of this multi-center trial is to determine the feasibility and safety of optimized tDCS stimulations with optimized electrode placements to improve swallowing function in patients with post-stroke dysphagia. By utilizing individualized three-dimensional brain models based on MRI scans, we aim to optimize electrode placement. Employing small-sized electrodes (1.5 cm radius) we further aim to increase the focality of the electrical field, allowing for precise targeting of cortical regions involved in swallowing function. This comprehensive, multi-center trial, involving four participating centers and stratifying patients based on age, chronicity, and center, aims to increase the generalizability of our findings. The assessment of a variety of dysphagia-related outcomes will provide a comprehensive evaluation of the treatment's impact. The integration of computational modeling with the application of small-sized electrodes presents an innovative strategy that could significantly improve rehabilitation outcomes for patients with post-stroke dysphagia.

Dysphagia significantly impacts the quality of life and increases mortality rates in post-stroke patients (4, 16). According to research, tDCS has the potential to become an added intervention for the improvement of swallowing dysfunction (4, 59). However, systematic reviews indicated that multicenter randomized controlled trials (RCT) with large populations are needed to draw more accurate conclusions about the effect of tDCS on the improvement of dysphagia, but especially to determine the best tDCS protocol to achieve it (4). As a multicenter RCT focused on optimizing tDCS electrode positions, the present study is crucial for the future use of tDCS in dysphagia rehabilitation.

Past research has used anodal tDCS over the lesioned side to treat dysphagia, finding improvement in the swallowing function (60, 61). Targeting the ipsilesional side might increase the activity of the lesional hemisphere and decrease the transcallosal inhibition exerted by the contralesional hemisphere, which is believed to be hyperactive after stroke (61). Additionally, some studies have suggested that targeting the ipsilesional motor region could reactivate intact portions of the motor cortex (62). Other research has shown that after stroke, compensatory reorganization of the contralesional hemispheric projections influences the recovery of swallowing function and therefore, some studies have applied anodal stimulation to the contralesional side (15, 63). Both anode locations have been shown to affect the improvement of the swallowing function positively. Based on evidence from Suntrup et al. (64), that post-stroke dysphagia recovery involves neuroplasticity in the intact hemisphere, we will apply anodal tDCS to the non-lesional hemisphere to enhance swallowing function.

While current research has shown the potential of tDCS for improving swallowing dysfunction in post-stroke dysphagia patients, to the best of our knowledge, research has yet to consider individual brain anatomical structure when determining the optimal tDCS electrode placement for tDCS intervention protocols in these patients. According to research, the conventional approach involves using the 10–20 EEG system to position tDCS electrodes over the cortical swallowing area, typically by identifying the midpoint between C3 and T3 or C4 and T4 (depending on the lesioned hemisphere) to stimulate the swallowing cortex. However, the 10–20 EEG system placements, although approximations to the targeted area, do not account for inter-individual variations in brain structures, such as skull thickness and gray and white matter integrity (65). Calculating an optimized electrode location offers a personalized electrode setting per participant, giving the exact location predicted to generate the maximum E-field over a targeted area.

In addition to the electrode location, tDCS effects are believed to be influenced by electrode shape and size. The majority of tDCS studies in patients with post-stroke dysphagia typically employed 25 cm^2^ electrode size (16, 60, 66, 67). Computer simulation studies evidenced that larger electrodes tend to stimulate broader brain regions, resulting in a dispersed current density. Furthermore, these electrodes contribute to the edge effect, leading to a concentration of the current at the edges, notably at the corners of rectangular and square electrodes (68). Employing smaller, circular-shaped electrodes may mitigate the edge effects and refine the precision of the current targeting at the intended area; therefore, disk electrodes of 1.5 cm will be used for the present trial.

For the present study protocol, we hypothesize that the optimized-tDCS group will show significant improvement in swallowing function compared to the Sham group, demonstrating the feasibility of using optimized electrode locations for tDCS stimulation for post-stroke dysphagia. Additionally, we hypothesize that all the participants will complete the intervention without any significant adverse effects after using optimized tDCS electrode location.

This study is significant in its assessment of the safety and efficacy of a personalized, focal tDCS approach using small-sized electrodes guided by each patient's individual brain computational modeling. By optimizing electrode placement for each participant, we aim to enhance both the therapeutic precision and safety of tDCS for post-stroke dysphagia. There are some potential limitations to disclose. First, there is currently no prior clinical evidence directly validating the safety of the specific electrode size proposed in this study. However, a preliminary computational model comparing E-field strengths using different size electrodes is being carried out (69). Also, the findings of this clinical trial will help address this gap by providing preliminary safety data. Second, while this is an exploratory trial, its value lies not only in demonstrating feasibility and safety, but also in establishing a foundation for a subsequent pivotal trial aimed at evaluating therapeutic efficacy on a larger scale. Additionally, our study included both ischemic and hemorrhagic stroke patients without subtype stratification. While our study included both ischemic and hemorrhagic stroke patients without subtype stratification, we deem that this approach was appropriate for a pilot feasibility study and reflects real-world clinical heterogeneity, though future definitive trials may benefit from pre-planned subtype stratification based on these preliminary findings. Our stratification by stroke onset time and age addresses more mechanistically relevant predictors of tDCS response than stroke etiology, particularly given our non-lesional hemisphere targeting approach. Furthermore, this mixed population methodology is consistent with major systematic reviews and meta-analyses that routinely treat stroke as a homogeneous condition without subgroup analysis by etiology (3, 4) and is supported by evidence showing comparable tDCS safety profiles between stroke subtypes. Ultimately, the outcomes of this study will inform future clinical trials and contribute to the development of more effective, personalized neurostimulation treatments.

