**Study outcome(s):**

The primary outcome measurements are the Functional Oral Intake Scale (FOIS) and the Penetration-aspiration Scale (PAS) together with various secondary outcomes, that include the Videofluoroscopic Dysphagia Scale (VDS) and other ancillary parameters that include voice quality and cough strength.

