**Discussion:**

We hypothesize that the active tDCS group will demonstrate significant improvements in swallowing function compared to the sham group, establishing the feasibility of personalized, focal-electrode interventions for post-stroke dysphagia rehabilitation.

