This double-blind, randomized pilot trial aims to determine the feasibility and safety of optimized transcranial direct current stimulation (tDCS) in patients with post-stroke dysphagia. Specifically, we will (1) evaluate the feasibility of using small-sized and optimized electrode placement to maximize E-field strength in the swallowing motor cortex—comparing active vs. sham stimulation, and (2) assess the clinical safety of this approach in post-stroke dysphagia patients.

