### Primary outcomes

#### Functional Oral intake Scale (FOIS)

The FOIS scale will be assessed as a primary outcome during the baseline and post-intervention periods. FOIS is a reliable and valid ordinal scale widely used for clinical and research purposes to assess changes in functional oral intake of food and liquids in patients with oropharyngeal dysphagia. FOIS is sensitive to changes in oral intake of food and liquid over time in stroke patients. This characteristic is essential when documenting overall stroke recovery or for detailed improvement associated with rehabilitation efforts. The scale ranges from level 1 (nothing by mouth) to level 7 (a full unrestricted oral diet) (31, 32).

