#### Penetration-aspiration Scale (PAS)

As a primary outcome, PAS will be assessed at Baseline and Post-intervention. The PAS is a standard scale to assess clinical practice and research deglutition. It is composed of an 8-point scale used to characterize the location of airway invasion events and the patient's response during videofluoroscopic swallowing studies. The scale was designed to capture three constructs: depth of airway invasion, material remaining after swallowing, and patient's response to aspiration. The scale ranges from score 1 (Material does not enter the airway) to score 8 (Material enters the airway, passes below the level of the vocal folds, and no effort is made to eject) (33, 34).

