### Sample size estimates

Due to the feasibility nature of the study, the primary goal is to evaluate the safety, practicability, and preliminary effects of optimized tDCS stimulations with personalized electrode placement in patients with post-stroke dysphagia. Consistent with established guidelines for feasibility and pilot studies, a formal power calculation for efficacy was not performed. Instead, the sample size of 30 participants (15 per group) was determined based on practical considerations and precedent from previous studies in this field. Specifically, a similar previous study (16) demonstrated protocol feasibility and observed clinically relevant improvements in swallowing function among 28 participants (14 per group) undergoing a 20-session tDCS intervention. Our study adopts a comparable intervention schedule and aims to provide reliable estimates of key feasibility outcomes-including recruitment rates, adherence, and adverse event profiles-while also generating preliminary data on the variability and potential effect size of our primary and secondary outcome measures. These findings will be essential for informing the design and sample size calculation of a future, large-scale randomized controlled trial.

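### The main hypothesis reads feasibility of optimized electrode placement from a significant active-versus-sham swallowing difference, which cannot show or refute it

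*Protocol article*

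**What the plan says.** **Aim.** The Introduction says the trial "aims to determine the feasibility and safety of optimized transcranial direct current stimulation (tDCS) in patients with post-stroke dysphagia". Its first specific aim places the feasibility evaluation within a comparison of active with sham stimulation.

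**Primary outcomes.** Both are swallowing scales: "The FOIS scale will be assessed as a primary outcome during the baseline and post-intervention periods", and "As a primary outcome, PAS will be assessed at Baseline and Post-intervention".

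**Main hypothesis.** The Discussion expects that "the optimized-tDCS group will show significant improvement in swallowing function compared to the Sham group, demonstrating the feasibility of using optimized electrode locations". The abstract makes the same step, with a significant advantage over sham "establishing the feasibility of personalized, focal-electrode interventions for post-stroke dysphagia rehabilitation". The next sentence of the Discussion gives a second, separate hypothesis: that every participant will finish the intervention without significant adverse effects.

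**Sample size.** The section "Sample size estimates" says that "the primary goal is to evaluate the safety, practicability, and preliminary effects of optimized tDCS stimulations" and that "a formal power calculation for efficacy was not performed". It sets 15 participants per group on practical grounds and precedent. It names recruitment, adherence and adverse events as the feasibility outcomes to be estimated.

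**What differs between arms.** The abstract's method paragraph and the section on individualized 3D brain modeling give both arms MRI-based modelling and personalised optimized electrode positions. The section on transcranial direct current stimulation says the sham arm has the same ramps without the current being held at 2 mA.

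**The concern.** Feasibility asks whether the procedure can be carried out: whether patients enrol, undergo imaging and modelling, attend the sessions and complete the assessments. The main hypothesis answers this with a test of whether the current improves swallowing, which is a different question. The article also declines to power the study for that test.

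Two misreadings of the result become possible. A procedure delivered without difficulty could be reported as lacking its expected demonstration of feasibility because a small efficacy comparison missed significance. Conversely, a significant swallowing result could be reported as showing feasibility even if recruitment or attendance had been poor. The findings are meant to inform the design and size of a later large trial, so an unsound feasibility statement would be carried forward.

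**Working it through.** **1. What the comparison can identify**

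| Element | Active | Sham |
|---|---|---|
| Baseline MRI and 3D model | yes | yes |
| Individually optimized electrode positions | yes | yes |
| Ramp-up and ramp-down | yes | yes |
| Current held at 2 mA | yes | no |

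Only the last row differs. A between-arm difference in FOIS or PAS therefore estimates an effect of the maintained current. Whether optimized placement can be delivered is the same question in both arms, and its natural denominator is all 30 participants.

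**2. Where the named feasibility outcomes appear**

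| Outcome named under "Sample size estimates" | Primary or secondary outcomes | "Statistical analysis" | Elsewhere |
|---|---|---|---|
| Recruitment | no | no | none |
| Adherence | no | no | completion appears in the second hypothesis |
| Adverse events | no | no | own section, reported by group |

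**3. How often the efficacy test would miss significance**

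The plan has no power figure to reproduce. Inputs from the plan are n = 15 per arm, 1:1 allocation and a two-sample t-test (Wilcoxon if normality fails). My assumptions are two-sided alpha of 0.05, no dropout, and a range of standardised differences d. The article gives no alpha, effect size or SD.

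- Degrees of freedom: 2 × 15 − 2 = 28; critical value 2.048.
- Noncentrality: d × √(15/2) = 2.739 d.
- Power: the probability that |T| exceeds 2.048 under the noncentral t distribution.

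| d | Noncentrality | Power | Missed |
|---|---|---|---|
| 0.3 | 0.82 | 12.5% | 87.5% |
| 0.5 | 1.37 | 26.2% | 73.8% |
| 0.8 | 2.19 | 56.2% | 43.8% |
| 1.0 | 2.74 | 75.3% | 24.7% |

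Power reaches 80% only at d = 1.06. Losing one participant per arm (n = 14) lowers it to 24.7% at d = 0.5 and 53.1% at d = 0.8. By the normal approximation, 80% power needs n per arm = 2(1.960 + 0.842)²/d², which is 63 at d = 0.5 and 25 at d = 0.8. Adjustment for baseline, which the plan also lists, would act like a larger d in this table.

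**4. What 30 participants can say about feasibility directly**

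Exact (Clopper-Pearson) 95% intervals for the share of participants completing:

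| Completing | Share | 95% CI |
|---|---|---|
| 30/30 | 100% | 88.4% to 100% |
| 27/30 | 90% | 73.5% to 97.9% |
| 24/30 | 80% | 61.4% to 92.3% |

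The intervals are wide, but they address the stated question and do not depend on whether the current works.

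**The case against.** The sentence in the Discussion is introduced as a hypothesis, and the Methods contain no rule that accepts or rejects feasibility on FOIS or PAS. The primary goal includes preliminary effects, so clinical scales as primary outcomes are a defensible choice. A pilot needs no efficacy power calculation, and the article is open about having none. It also calls the trial exploratory and leaves efficacy to a later pivotal trial. All of this stands.

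It limits several stronger readings that a reader might infer:

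- **That feasibility and safety get no valid answer.** The documents do not support this. Adverse events are assessed during and after each session, classified, coded and reported by group, and the second hypothesis covers completion and adverse effects. Recruitment and adherence are named as quantities to estimate, so a descriptive feasibility answer remains possible.
- **That a swallowing p-value is the only decision rule, or that it decides whether the pivotal trial proceeds.** No passage says so. The findings are to inform the later trial's design and sample size.
- **That low power is itself the error.** It is not. The power figures matter only because a feasibility statement has been attached to the test.
- **That missing progression thresholds, or missing multiplicity rules for two primary scales, are faults.** Both are commonly left to the full protocol or analysis plan, which are not shown.

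By the same reasoning, the absence of recruitment and adherence from the outcome sections would be minor in a condensed article. It matters here because the main hypothesis puts an efficacy result in their place. None of these points rescues the inference itself, which is stated in two places and is unsound in either direction.

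**Conclusion.** The concern holds in a limited form. The abstract and Discussion tie feasibility of optimized placement to a significant active-versus-sham swallowing difference. Because both arms receive the same placement, that difference does not measure feasibility whichever way it falls. This conclusion rests on the design alone and needs no assumption about effect size.

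The size of the practical risk does depend on assumptions. With two-sided 5%, 15 per arm, no dropout and an approximately normal outcome, the test would miss significance about 74% of the time at d = 0.5 and 44% at d = 0.8, however smoothly the procedure was delivered. FOIS and PAS are ordinal, so these percentages are a guide and not a prediction. The safety analysis is unaffected. What is needed is a correction of wording and alignment that changes what the trial may conclude.

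**What to change.** 1. Remove from the abstract and the Discussion the statement that a significant swallowing improvement demonstrates or establishes feasibility. State the efficacy expectation and the feasibility objective as separate sentences.
2. List the feasibility outcomes among the outcomes and in the analysis section: recruitment rate, share of the 20 sessions completed, and completion of the post-intervention assessment (V24). Report each with an exact 95% confidence interval, alongside adverse events by arm. Base these intervals on participants: 30 × 20 = 600 sessions are not 600 independent observations.
3. Report FOIS and PAS as preliminary between-arm differences with 95% confidence intervals, for use in planning the later trial.

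Make the change before unblinding. It costs edits to the article's wording and matching entries in the full protocol, analysis plan and registry. Treatment and visits stay as they are: Table 1 already schedules screening numbers, 10 + 10 = 20 session visits, adverse-event checks and V24. The downside is that an efficacy p-value can no longer be used to claim feasibility.

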## Summary and conclusions

Post-stroke dysphagia is a common complication which may adversely affect patients' long-term prognosis. Although tDCS has demonstrated therapeutic potential in prior studies, its efficacy may be further enhanced through personalized and optimized stimulation techniques. This study protocol introduces a novel approach with individualized electrode placement, refined cortical targeting, and a rigorous methodological framework. By addressing limitations in earlier trials and integrating computational modeling and focal stimulation techniques, the study aims to improve swallowing outcomes in individuals with post-stroke dysphagia and establish tDCS as a clinically viable treatment strategy. Findings from this study will provide critical data to support the planning and implementation of larger, multi-center RCT.
